### Study protocol

Eligible patients will be initially evaluated by their medical history, prior HFpHF diagnosis, physical tests, resting electrocardiogram, two-dimensional echocardiogram, protocols of pulmonary function and inspiratory muscle function, cardiopulmonary exercise testing (CPET), 6-min walk test, Minnesota QoL, N-terminal pro b-type natriuretic peptide (NT-proBNP), and HRV frequencies (Holter 24 h). All of these evaluations will be detailed in the appropriate sections. These records and personal information will be securely stored in HCPA facility and accessed only by assistants and researchers.

After signing informed consent and pre-test intervention forms, patients will be randomized into three groups as follows (Fig. 1). The present protocol followed the SPIRIT guidelines and fulfilled the SPIRIT checklist (Additional file 1):

**Fig. 1 Fig1:**
[figure not shown]
Flowchart of study participation and intervention

#### Yoga – active breathing technique

Active protocol with yoga body movements (*àsanas*) performed along with respiratory technique without contentions, current and vigorous (*ujjayi*), observing a respiratory frequency of 15–20 respiratory cycles per minute. This session should last around 45 min.

#### Yoga – passive breathing technique (*pranàyama*)

Passive protocol, seated patient, no significant body movements. Yoga breathing technique with alternate nostril breathing (*viloma pranàyama*) uses diaphragmatic breathing, both current and combined with inspiratory and expiratory retentions, observing a slow respiratory frequency of between 5 and 8 respiratory cycles per minute. This session will last approximately 45 min.

A standardized 7-min final relaxation will be performed and will be common to both study intervention protocols.

#### Control group (standard pharmacological treatment)

Patients will be oriented to keep their pharmacological routine and daily activities with no structured exercises. They will have to return to the hospital for post-testing after 8 weeks of randomization. After final assessment, all patients, including those in the control group, will be invited to participate in the study breathing activities at the outpatient wards of this trial.

Intervention will last 8 weeks (16 sessions). The post-intervention tests will be performed at the end of the intervention period for the evaluation of endpoints (Fig. 2). To ensure security, data will be stored both in the main researcher’s and study coordinator’s computers, as well as being added to a virtual drive. Researchers, study coordinators, doctors, and statisticians will be allowed data access. Interventions will occur at specific facilities in HCPA (physiatrist sector) and in ULBRA University hospital (medical school) according to patient enrollment. Protocol deviation and adverse events involving individual participants in clinical studies in the HCPA are recorded in the strategic adviser system available in the hospital intranet. Deviations and adverse events occurring at ULBRA will be recorded in the same system as the HCPA. The auditing procedures will occur randomly or designated by the ethical committee for research analysis.

**Fig. 2 Fig2:**
[figure not shown]
Schedule of enrollment, interventions, and assessments

The HFpEF diagnosis will be performed by trained cardiologist experts in the HF field according to the following criteria: HF patient showing an ejection fraction ≥ 50% and E/E’ index of > 8. In addition, other data will be considered for diagnosis, such as left atrial volume > 40 mL/m^2^, atrial fibrillation, and left ventricular mass index. The diagnosis will be confirmed by B-type natriuretic peptide (BNP) levels > 200 pg/mL or NT-proBNP > 220 pg/mL. Patients will be classified either as HFpEF with pseudonormal filling pattern (moderate, grade II) when 8 < E/E’ < 15; or as HFpEF with restrictive left ventricular filling pattern (severe, grade III) when E/E’ > 15. The HF functional classification will be assessed by the New York Heart Association (NYHA) classification system.

#### Pulmonary function

Inspiratory muscle function testing will be performed using a pressure transducer (MVD-500 V.1.1 Microhard System, Globalmed, Porto Alegre, RS, Brazil) connected to a system with two unidirectional valves (DHD Inspiratory Muscle Trainer, Chicago, Illinois, USA). Maximal static inspiratory pressure will be determined in deep inspiration from residual volume against an occluded airway, with a minor air leak (2 mm). The highest pressure within six measurements will be used for analysis. The PI_max_ measurement will be performed at rest and at the 5th and 10th min after CPET. Predicted values will be corrected for age, sex, and weight [14]. Additionally, in order to determine the inspiratory muscle endurance, an incremental test will be used in which patients will breathe continuously through a mouthpiece connected to a measure device. The patients will use an initial load of 50% PI_max_, and increments of 10% PI_max_ will be added every 3 min until the patient is unable to continue breathing. The highest inspiratory pressure that the individual is able to sustain for at least 1 min (Pth_max_) will be considered as the measure for inspiratory muscle endurance and will be expressed as a rate of maximal inspiratory pressure (Pth_max_/PI_max_). In the second stage of the protocol, individuals will breathe against a constant inspiratory submaximal load equivalent to 80% Pth_max_, and the time elapsed to task failure will be defined as the inspiratory endurance time. The Powerbreathe K5 will be used for patients with IMW and for those with normal respiratory fraction, for age and sex [15, 16].

#### Six-minute walk test

The maximum distance covered during the walk test will be used to assess submaximal functional capacity [19]. Patients will self-grade their degree of dyspnea during the test using the Borg scale [20].

#### Cardiopulmonary exercise testing

Maximal functional capacity will be evaluated using an incremental exercise test, with expired gas analysis, on a treadmill (INBRAMED10200, Porto Alegre, RS, Brazil), using a ramp protocol, starting at a speed of 2.4 km·h^− 1^ and 2% slope, with 20-s increments of speed (0.1 to 0.2 km·h^− 1^) and 60-s increments in slope (0.5% to 1.0%) to reach volitional fatigue at approximately 10 min. Twelve-lead electrocardiographic tracings will be obtained every minute (Nihon Khoden Corp., Tokyo, Japan). Blood pressure will be measured every 2 min with a standard cuff sphygmomanometer. Metabolic and ventilatory variables will be measured along and after exercise by 20-s mean aliquots, by a computer-aided gas analyzer (Total Metabolic Analysis System, TEEM 100, Aero Sport, Ann Arbor, Michigan, USA), previously validated [21]. Peak oxygen uptake (VO_2_ peak) will be considered as the highest VO_2_ value calculated in a 20-s period exercise. Maximal circulatory power will be calculated as the product of VO_2_ peak and peak systolic pressure [22]. Throughout incremental exercise, oxygen uptake will be plotted against the logarithm of total ventilation, and the oxygen uptake efficiency slope will be determined [23].

#### QoL

QoL will be assessed using the Minnesota Living with Heart Failure Questionnaire [24]. Overall scores and the separate effects of physical and psychological perceptions of QoL will be analyzed.

#### HRV analysis

Twenty-four-hour ECG recordings will be obtained with a SEER Light digital recorder (GE Medical Systems Information Technologies, Milwaukee, WI, USA). The recorded data will be analyzed using a MARS 8000 analyzer (Marquete Medical Systems, Milwaukee, WI, USA) [25, 26]. Briefly, time domain and frequency domain analyses of HRV will be performed according to the recommended by the European Society of Cardiology and North American Society of Pacing and Electrophysiology [27]. For time domain analysis, the following 24-h indices will be calculated: mean of all normal inter-beat (RR) intervals, standard deviation of all normal RR intervals, root mean square of successive differences of adjacent RR intervals, and rate of successive differences between normal adjacent RR intervals above 50 ms. For frequency domain analysis, the following spectral components will be calculated: low frequency (0.04–0.15 Hz), high frequency (0.15–0.5 Hz), and low-to-high frequency ratio. Spectral components will be expressed in absolute values (ms^2^ Hz) and in normalized units. Heart rate spectral analysis and time domain indices will be calculated using 5-min segments at rest during active breathing (*ujjayi*) and passive breathing (*pranàyama).*

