### Endpoints

The primary endpoints are inspiratory muscle strength by measuring maximal inspiratory pressure (PI_max_).

Secondary endpoints include (1) vagal activity in resting and exercising (HRV); (2) peak VO_2_; (3) QoL Minnesota scores as a specific inventory for patients with HF; (4) functional capacity (NYHA Classification); (5) volumetric ratios of left atrial and diastolic pressure gradients on echocardiography; and (6) changes in BNP/NT-proBNP tests between pre- and post-intervention measurements.

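### The 5-min HRV indices are taken during techniques whose breathing rates fall in different spectral bands, so they should not carry the between-arm comparison of vagal activity

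*Protocol article*

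**What the plan says.** All references are to the protocol article.

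- **HRV analysis, recording condition:** "Heart rate spectral analysis and time domain indices will be calculated using 5-min segments at rest during active breathing"; the sentence goes on to name passive breathing as well. No condition is stated for controls.
- **HRV analysis, spectral components:** "low frequency (0.04–0.15 Hz), high frequency (0.15–0.5 Hz), and low-to-high frequency ratio", reported in absolute and normalized units.
- **HRV analysis, long recording:** "For time domain analysis, the following 24-h indices will be calculated", followed by the mean and SD of normal RR intervals, RMSSD and the rate of successive differences above 50 ms.
- **Study protocol:** the pre-test list includes "HRV frequencies (Holter 24 h").
- **Yoga – active breathing technique:** "observing a respiratory frequency of 15–20 respiratory cycles per minute".
- **Yoga – passive breathing technique:** "observing a slow respiratory frequency of between 5 and 8 respiratory cycles per minute".
- **Control group:** usual drugs and daily activities, with no breathing technique.
- **Endpoints:** the first-listed secondary endpoint is "vagal activity in resting and exercising (HRV"), with neither index nor segment named.
- **Statistical analysis:** a GEE model compares means across three groups and two times, with a group × time term.

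**The concern.** LF and HF are fixed frequency windows. The heart-rate oscillation driven by breathing appears at the breathing frequency, so the window that counts it depends on how fast the patient breathes. If the two yoga arms are recorded at rates on opposite sides of the LF/HF limit, the same respiratory oscillation is counted as HF in one arm and LF in the other. Controls, with no prescribed technique, supply neither condition.

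The Background itself notes that breathing rate and amplitude strongly affect beat-to-beat variability. What is at stake is interpretation: a large, statistically clear difference in LF/HF could be reported as an autonomic benefit of eight weeks of training when it shows only what patients were doing during the recording.

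**Working it through.** The plan gives no figure to reproduce here. The check converts breathing rates to frequencies and compares them with the stated bands.

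**1. Rates to frequencies.** Frequency in Hz = breaths per minute / 60.

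| Technique | Prescribed rate | Frequency | Band |
|---|---|---|---|
| Active (ujjayi) | 15–20/min | 15/60 = 0.250 to 20/60 = 0.333 Hz | HF (0.15–0.5 Hz) |
| Passive (pranayama) | 5–8/min | 5/60 = 0.083 to 8/60 = 0.133 Hz | LF (0.04–0.15 Hz) |

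The limit between the bands is 0.15 × 60 = 9 breaths/min. LF starts at 0.04 × 60 = 2.4 and HF ends at 0.5 × 60 = 30 breaths/min. Both prescribed ranges lie wholly inside one band, on opposite sides of the limit.

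**2. Does the group × time term remove this?** The Randomization section places allocation after the pre-intervention tests, so a pre-test segment cannot be recorded in the patient's own arm's technique. If the pre-test is at spontaneous breathing and the post-test is in the assigned technique, the acute change in breathing rate falls into the interaction and is not cancelled by it.

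**3. Illustration of size.** All powers are assumptions. Let non-respiratory LF power be 1, non-respiratory HF power 0.2, and respiratory power R, identical in both arms.

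- Active: LF/HF = 1 / (0.2 + R)
- Passive: LF/HF = (1 + R) / 0.2

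| R | Active | Passive | Passive / active |
|---|---|---|---|
| 0.5 | 1/0.7 = 1.43 | 1.5/0.2 = 7.5 | 5.25 |
| 1 | 1/1.2 = 0.83 | 2/0.2 = 10 | 12 |

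**4. Sensitivity to the assumptions.** Simulated 5-min RR series were run with only the breathing rate changed (assumed respiratory amplitude 10–30 ms, 0.1 Hz component 10–20 ms, noise SD 10 ms). LF/HF was about 6 to 37 at 5–8 breaths/min and about 0.1 to 3 at 15–20. HF in normalized units was about 3–14% against 25–89%. For matched amplitudes the ratio of LF/HF ran from about 14.59/3.06 = 4.8 to about 28.49/0.12 = 237. The direction is the same throughout, while the size depends heavily on what is assumed.

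**5. What the check does not reach.** The 24-h time-domain indices are not confined to technique segments, so the band argument does not apply to them. Time-domain indices from the 5-min technique segments have no band to cross, but they share the unmatched recording condition.

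**The case against.** The strongest reply is that the article does not make the technique segments the endpoint. The Endpoints section names only vagal activity measured by HRV, the HRV section also lists 24-h indices, and the pre-test list takes HRV frequencies from a 24-h Holter. This stands. A reader might infer that the whole vagal-activity endpoint differs between arms by construction, but the document does not support that.

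Second, recording in the arm's own technique is the natural reading, not a stated rule. The sentence could mean that every patient performs both techniques, or that rest, active and passive breathing are three separate conditions. Were every patient recorded in both techniques, arms could be compared within a technique and the confounding by prescribed rate would go. This too stands, as a condition on the conclusion.

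Third, describing the acute response may be intended; the Discussion mentions acute as well as adaptive responses. That is a legitimate aim, but it calls for within-arm description, and nothing in the text keeps these segments out of the three-group comparison.

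It might also be said that such detail belongs in an analysis plan. Here, however, the article states a recording condition, and the objection is to that statement rather than to an omission.

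A reader might further infer that recordings in atrial fibrillation would spoil the HRV results, since that rhythm supports the diagnosis (Study protocol) and is not an exclusion. The article gives no frequency for it, and the handling of non-sinus recordings is commonly left to the full protocol or analysis plan. It is a side remark only.

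**Conclusion.** The point holds for the 5-min spectral indices. LF, HF, LF/HF and normalized units recorded during the techniques are confounded with breathing rate between the yoga arms, and controls have no matching condition. Such differences cannot be read as a training effect on vagal activity. This rests on two premises: each yoga arm is recorded in its own technique, and those segments enter the between-arm comparison. The first is the natural reading; the second is not excluded by the text.

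The band placement follows directly from the article's own numbers. The 5- to 12-fold gap in LF/HF is an illustration under assumed powers, not an estimate for this trial. The issue is confined to part of one secondary endpoint: the 24-h time-domain indices escape it, and the primary endpoint, maximal inspiratory pressure, is untouched. It is worth correcting before analysis, but it does not threaten the trial's main result.

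**What to change.** Name the HRV index used for the between-arm comparison and base it on 5-min segments at rest with spontaneous breathing, taken under the same condition in all three arms at both visits. These can be selected from the 24-h Holter recordings the protocol already provides for. Analyse them together with the 24-h time-domain indices already listed. Report segments recorded during ujjayi and pranayama as within-arm description only, and say at which visit and in which patients they are taken. As a side remark, a line on how recordings in atrial fibrillation are handled would help.

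The cost is a change of wording plus a little extra segment selection and analysis. The Trial status section reports 20 patients enrolled and 18 completed, so for these the segments would have to come from stored recordings. The selection rule should be fixed before arms are compared.

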#### BNP and NT-proBNP

Since this trial will be performed at two centers, both BNP or NT-proBNP methods will be used, yet the same biomarker (either BNP or NT-proBNP) will be employed for pre- and post-tests in any given patient. The BNP test will be performed on the clinical specimen using blood serum and a chemiluminescence analysis method (Advia Centaursiemens). The NT-proBNP test will be performed on a clinical specimen using blood serum and a sandwich-type electrochemiluminescence analysis method (Cobas E601-Roche).

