### Randomization

Patients who meet the eligibility criteria will be invited to participate in the study; those who accept to participate will sign a written informed consent form. Following the conclusion of pre-intervention tests, the researcher will inform the biostatistics center at HCPA, which is in charge of the randomization list, and participants will be allocated to either yoga (active) or yoga (passive) or control group in a 1:1:1 ratio using a pre-generated simple randomization list.

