### Statistical analysis

Initially, a descriptive analysis will be performed and data will be expressed as absolute and relative frequency, besides mean and standard deviation or quartiles, accordingly. The treatment groups will be compared using the generalized estimating equation, specific for repeated measurements, in order to compare the effects (means) across the three groups and the two times, in addition to the group × time interaction. The generalized estimating equation matrix of robust estimator covariance and exchangeable work correlation matrix will be used if normal distribution is found and will be analyzed by an identity binding function. In contrast, if an asymmetrical distribution is found, data will be analyzed using a gamma distribution linked to a logarithmic function. When significant, the factors under study will be compared by Bonferroni’s post-hoc test. Correlations will be described by the Pearson’s or Spearman’s test. The PASW18 (version 18.0, SPSS, Chicago, Illinois, USA) will be used in this analysis.

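### BNP and NT-proBNP form one secondary endpoint analysed by one means model with no assay term, so as written the comparison combines two scales

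*Protocol article*

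**What the plan says.** All references are to the Protocol article.

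- **BNP and NT-proBNP**: with two participating centres, "both BNP or NT-proBNP methods will be used, yet the same biomarker (either BNP or NT-proBNP) will be employed" at both tests. The rule holds within a patient; different patients may have different markers. The two assays run on different platforms. The section does not say which centre uses which.
- **Endpoints**: the sixth secondary endpoint is "changes in BNP/NT-proBNP tests between pre- and post-intervention measurements", a single item covering both markers.
- **Statistical analysis**: one GEE is used "in order to compare the effects (means) across the three groups and the two times, in addition to the group × time interaction". It has an identity link if the data are normal and a gamma distribution with log link if they are asymmetrical. No assay or centre term, conversion or separate analysis by assay is mentioned.
- **Randomization**: patients are allocated 1:1:1 "using a pre-generated simple randomization list", with no stratification by centre stated.
- **Study protocol** (diagnostic criteria after Fig. 2): each marker has its own threshold, above 200 pg/mL for BNP and above 220 pg/mL for NT-proBNP.

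The list of initial evaluations in Study protocol names only NT-proBNP, which does not fit the two-marker rule and should be aligned with it.

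**The concern.** Holding the marker fixed within a patient keeps that patient's own before-after comparison coherent. It does not make a pg/mL change on one assay equal to a pg/mL change on the other once changes are averaged over patients in an arm. The separate diagnostic thresholds suggest that the protocol itself does not regard the two as one quantity.

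Two things are at stake. First, the arm means, and any absolute change between them, depend partly on how many patients in each arm had which assay. Since the protocol attributes the two markers to the two centres and the randomization list is simple, that mix is left to chance among 33 patients. Second, patients measured on the lower-reading assay carry less weight than their number warrants, so an already small comparison loses information.

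**Working it through.** The documents give no effect size, SD or power for this endpoint, so there is no plan figure to reproduce.

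**Inputs from the documents:** 33 patients, 11 per group (Abstract; Sample size); three groups, two times, GEE on means (Statistical analysis); simple 1:1:1 list (Randomization).

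**Assumptions, not in the documents:** k, the ratio of typical values on the higher-reading assay to those on the lower-reading one in comparable patients; the share p of patients on the higher-reading assay; and the relative changes and variabilities used below.

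**1. Weight of the lower-reading patients.** Take an even split, with equal relative change and equal relative variability on both assays. Raw changes then scale as 1 to k and their variances as 1 to k². In an arm's mean change relative to its baseline mean, each patient is weighted in proportion to level. The effective fraction of patients is therefore (1+k)²/(2(1+k²)), shown here out of 11.

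| k | Share of mean change, 1/(1+k) | Share of raw-change variance, 1/(1+k²) | Effective patients of 11 |
|---|---|---|---|
| 1.1 | 48% | 45% | 11.0 |
| 2 | 33% | 20% | 9.9 |
| 3 | 25% | 10% | 8.8 |
| 5 | 17% | 3.8% | 7.6 |
| 8 | 11% | 1.5% | 6.9 |

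The row k = 1.1 is 220/200, the ratio of the two diagnostic thresholds. That is not a conversion factor and serves only as a small-k reference.

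**2. Identity link with unequal assay mix.** Assume every patient in both arms falls by 20%, the lower-reading mean is 250 pg/mL, and p is 0.4 in one arm and 0.7 in the other. Mean change = −0.2 × 250 × (1 − p + pk).

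- k = 1: −50 vs −50, difference 0.
- k = 2: −0.2 × 350 = −70 vs −0.2 × 425 = −85, difference 15.
- k = 4: −0.2 × 550 = −110 vs −0.2 × 775 = −155, difference 45.
- k = 8: −0.2 × 950 = −190 vs −0.2 × 1475 = −295, difference 105 pg/mL.

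The relative effect is identical in both arms. If the common fall is set to 0, every difference is 0 whatever the mix.

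**3. Log link, same example.** At k = 4 the post/pre ratios of means are 440/550 = 0.80 and 620/775 = 0.80. The scale factor cancels from group × time for every k. It does not cancel from the group main effect or the level means. If relative effects differ between patients, the higher-reading assay carries k/(1+k) of an evenly split mean: 67%, 80% and 89% at k = 2, 4 and 8.

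**4. How often the mix differs.** In 20,000 simulated simple randomizations of 33 patients to three groups, the largest gap in assay share between any two arms was at least 20 percentage points in 65% of runs when about half the patients had each assay, and in 62% when the split was 70/30. It was at least 30 points in 39% and 33%.

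**5. Illustrative power.** Assume 11 per arm, a 30% fall against none, log SD of change 0.4, baseline log SD 0.6 and an even chance of each assay. A t-test on raw change has power 37%, 35%, 27% and 23% at k = 1, 2, 4 and 8. A test on the within-patient log change has 51–53% throughout. The drop from 37% to 23% is due to mixing scales. The gap already present at k = 1 comes from analysing assumed log-normal data on the raw scale.

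**The case against.** No sentence says that raw values from the two assays will be put together. The Endpoints item may be shorthand for whichever marker a patient had, and Statistical analysis is one generic paragraph for all endpoints. A full protocol or SAP, not shown, might separate the assays. That stands as a limit: combination is inferred. But one endpoint, one means model and no assay term leave it as the natural reading of what is written.

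A reader might infer that the analysis is simply an identity-link comparison of pg/mL. The text does not support that. The identity link is conditional on normality, and data mixed from two well-separated scales could well be judged asymmetrical and sent to the gamma model, where a common relative effect cancels. The loss of precision and the unequal weighting remain.

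A reader might also infer that one centre's patients contribute almost nothing. That confuses a share of variance with a share of the estimate: at k = 8 the figures are 1.5% and 11%.

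Nor is the treatment comparison systematically biased. Imbalance under simple randomization is chance, and it distorts absolute changes only when the arms share a non-zero change. The differences of 15 to 105 pg/mL need both the assumed 20% fall, including in the control arm, and the assumed 40% against 70% split.

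**Conclusion.** The concern holds in limited form. As written, the plan defines one endpoint on two assays and compares its means with no term for assay. Under the identity link, the absolute changes being averaged are not commensurable, and a chance difference in assay mix can create or hide an arm difference in this one trial if there is a common change. Under the gamma/log link, group × time is protected when relative effects are equal, but the higher-reading assay dominates the means and information is lost.

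The size rests on k and the assay split, neither of which is in the documents. At an even split the loss is roughly 2 of 11 patients per arm at k = 3 and 4 of 11 at k = 8, and negligible near k = 1. This is one of six secondary endpoints. PImax, on which the trial was sized, is untouched.

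**What to change.** State in the analysis plan that the natriuretic peptide is analysed as the log of the 8-week value, adjusted for log baseline and for assay (or centre, if the two coincide). The within-patient log post/pre ratio with an assay term is an acceptable alternative. Report between-arm ratios of geometric means, show results separately by assay, and do not combine raw pg/mL values. In the example in step 2 this gives a between-arm difference of 0 on the log scale for every k.

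Also state which centre uses which assay, and align the list of initial evaluations in Study protocol with the two-marker rule.

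The cost is wording and a small change to the model. No new samples are needed. Trial status reports 20 patients enrolled of the 33 planned, so the change can still be fixed before the final analysis.
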